## **BACKGROUND**

Several modifiable risk factors related to the onset of type 2 Diabetes in women have been identified (1), and lifestyle changes, particularly the Mediterranean Diet (MedDiet), have proved to be effective in preventing its occurrence (2-3).

Gestational diabetes mellitus (GDM) is a growing health problem because of its increasing prevalence, its association with adverse pregnancy and birth outcomes (4) and because is an established risk factor for the development of type 2 diabetes and cardiovascular disease over longer term (5). The use of new criteria for diagnosing GDM, recommended after the HAPO study (6), has been associated with an increase in prevalence, i.e. from 8% (NDDG criteria) and 12.5% (Carpenter Coustan criteria) to 35% in a revaluation of our population of women (7). Despite the diagnosis of GDM with more stringent criteria, HAPO study shows a continuous association of maternal glucose levels below those previously used to GDM diagnosis with increased birth weight and adverse pregnancy outcomes. Regarding this dramatic increase in GDM diagnosis observed with the proposed IADPSG criteria, it is important to remember that previous criteria required two abnormal oral glucose tolerance tests. However, it has been demonstrated that women who had one abnormal test value and who were considered previously as "normal" had many of the outcomes that were similar to those who were as GDM.

Recently, based in a large population of more than 2000 women, our group has developed a risk appraisal model for GDM by identifying modifiable factors that can help to predict the risk of GDM (7). After logistic regression model, biscuits and pastries <4 times/week, red and processed meats intake < 6 serving/week, juices < 4 servings/ week, light walking >30 minutes/day and 30 minutes/day of physical activity of moderate intensity at least 2 days/week was associated with less GDM risk compared to the opposite. This data may represent a promising approach for the prevention of GDM and subsequent complications. In Spain, the Community of Madrid is one of the regions with higher foreigner rates, 18.8% of the total population (January 2011), with 49.7% of women. About 50% of pregnant women attended in our hospital during 2012 were immigrants. Recently, we have reported that this population tends to acquire the same risk factors as the Spanish population associated with lifestyle (8). Prepregnancy

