## **OBJECTIVES:**

### **Primary outcome:**

- To define the prevention of GDM (evaluated at 24-28 GWs with HAPO criteria) after the lifestyle intervention based on MedDiet and physical activity/exercise, as compared to standard treatment, in women with normal FPG (<92mg/dL) at the 1st gestational visit (8-12 GWs).

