### **SAMPLE SIZE CALCULATION**

For sample size calculation, a primary end-point for conversion to GDM has been used, assuming an expected conversion rate of 35% between 24-28 GWs and a reduction of at least 30% in the conversion to GDM after intervention. This intervention has shown a decrease of FPG -7 (-13; -1.3) mg/dl after 3 months in the PREDIMED Study (1), representing a potential reduction of GDM rate higher than 30%. A sample size of 315 women analyzed per group to provide statistical power of 80% to detect a 30% difference between groups in the primary outcomes at 5% significance. This number has been increased to **500 per group**, to allow for a predicted drop-out of around 20% (in accordance with the expected response rate, loss to follow up, lack of compliance, and any other predicted reasons for loss of subjects). Therefore, **1000 women will be randomized** in the study and we expect to assess at least 700.

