### ***Selection of Patients***

The Institutional Review Board and the Clinical Ethic Committee of the Hospital Clínico San Carlos have approved this protocol before initiation of the study (approval reference: CP.CI.13/296-E). We will include pregnant women who fulfill the inclusion criteria and none of the exclusion criteria. Subjects must give signed and dated informed consent (attached in a separate file) prior to any trial-related activities. Structure of the trial is displayed in ***Figure 1***.

Inclusion criteria: women >18 year old, with normal fasting glucose values (< 92 mg/dl) in the 1st gestational assessment (8-12 GWs) and sign the informed consent.

Exclusion criteria: women with fasting glucose levels  $\geq 92$  mg/dl in the 1st gestational assessment (8-12 GWs), multiple pregnancy, nut allergy, or any other reason, medical condition, ongoing medication or significant disability that would prevent the participant complying with trial consent, treatment and follow-up procedures or potentially jeopardize her medical care.

Figure 1 - Flowchart of the trial.

[figure not shown]

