## Final statistical analysis

### Sample size

For sample size calculation the primary end-point was the incidence of GDM between 24-28 GWs. We estimated that 315 women per group would be required to provide statistical power of 80% (2-tailed  $\alpha = 0.05$ ) to detect a relative risk reduction of at least 30% after intervention assuming an incidence of 35% GDM in the control group. Previously, this intervention has shown a decrease of the median of fasting blood glucose (FBG) -0.38 mmol/L after 3 months, representing a potential reduction of GDM rate higher than 30%. Taking into account loss to follow-up, we included 1000 successive women that attended their first ultrasound visit at the Obstetrics department between 12-14 GW, to guarantee a minimum duration of 12-weeks of intervention.

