### Statistical analysis.

Variables are presented with their frequency distribution. Quantitative variables are summarized by their mean and standard deviation ( $\pm$ SD). All primary analyses were performed on an intention-to-treat basis. Comparison between baseline group characteristics and primary and secondary outcomes for qualitative variables were evaluated by the chi-squared test. For quantitative variables, measures were compared through Student's t test or the nonparametric Mann-Whitney U test if the quantitative variables would not adjust to a normal distribution. The Shapiro-Wilk test was used to verify the normal distribution of data.

Logistic regression analyses were used to assess the effect of the intervention for the primary and secondary outcomes that were significantly different in the univariate analysis. The magnitude of association was evaluated using the odds ratio (OR) and 95% confidence interval (CI). A crude and 5 multivariate models were fitted: model 1 was adjusted for age (continuous) ethnicity and parity; model 2 adjusted for pregestational BMI and gestational weight gain (continuous); model 3 adjusted for gestational, personal and family history, and smoker status (never, current, or former smoker); Model 4 adjusted for the variables in Models 1 and 2; and Model 5, adjusted for the variables in Models 1-3. These models 4 and 5 were only fitted for the primary outcome due to the small number of events in many of the secondary outcome variables.

All *p* values are 2-tailed at less than 0.050. Analyses were done using SPSS, version 21 (SPSS, Chicago, Illinois).

ADENDUM April 01, 2017.

Statistical analysis.

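### Entry fasting glucose, required of every woman for eligibility, is in no listed adjusted model of the GDM outcome; adding it is a modest, nearly free efficiency gain

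*Protocol*

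**What the plan says.** **Eligibility.** *Selection of Patients* admits women "with normal fasting glucose values (< 92 mg/dl) in the 1st gestational assessment (8-12 GWs". There is no lower limit. The value therefore exists for every eligible woman before she is allocated.

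**Primary outcome.** The objective is "To define the prevention of GDM (evaluated at 24-28 GWs with HAPO criteria" after the lifestyle intervention. The HAPO cut-offs are not printed.

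**Link between the two.** *Sample size calculation* and the later *Sample size* section both take a fall in fasting glucose seen in an earlier trial (7 mg/dl, or 0.38 mmol/L) as pointing to a GDM reduction of more than 30%.

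**Analysis.** Under *Final statistical analysis*, the groups are compared by the chi-squared test. Then "A crude and 5 multivariate models were fitted: model 1 was adjusted for age (continuous) ethnicity and parity; model 2 adjusted for pregestational BMI". The second term of Model 2 is weight gain during pregnancy. Model 3 takes gestational, personal and family history and smoking. Model 4 combines Models 1 and 2, and Model 5 combines Models 1 to 3. The sentence introducing the logistic models ties them to outcomes that differed significantly in the univariate comparison.

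**Addendum of April 1, 2017.** It moves to relative risks (correction of the adjusted odds ratio, log-binomial, robust Poisson, robust Cox) and names no further covariate.

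**Randomisation.** *Intervention* stratifies by age, BMI and parity.

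**The concern.** A baseline measurement of the quantity that underlies a diagnosis is usually among its better predictors. Here it is also complete by design and free to use. Leaving it out has two consequences.

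- If the arms differ by chance in entry fasting glucose, no listed analysis can show how much of the GDM contrast that explains.
- If the value predicts GDM, the adjusted estimate is less efficient than it could be.

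This is not a detail left to a separate analysis plan, because the protocol's final analysis section lists the models and their covariates.

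**Working it through.** **1. The plan's own figure.** Inputs: "assuming an incidence of 35% GDM in the control group", and power "to detect a relative risk reduction of at least 30% after intervention", so p1 = 0.35 and p2 = 0.35 × 0.70 = 0.245. The difference is d = 0.105 and the mean is p̄ = 0.2975. Alpha is 0.05 two-sided and power is 80%.

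n = [1.960 √(2p̄(1−p̄)) + 0.842 √(p1(1−p1) + p2(1−p2))]² / d² = (1.267 + 0.541)² / 0.011025 = 296.4, so 297 per group.

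With continuity correction: (n/4)[1 + √(1 + 4/(nd))]² = 315.2, or 316 rounded up. This reproduces the stated 315 to rounding. The figure rests on an unadjusted comparison, so the planned power does not depend on the missing covariate.

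**2. Unadjusted power.** Power = Φ{[d√n − 1.960 √(2p̄(1−p̄))] / √(p1(1−p1) + p2(1−p2))}:

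- 315 per arm: 82.3%
- 350 per arm (half of the 700 the protocol expects at least to assess): 86.1%
- 400 per arm (500 less 20% drop-out): 90.3%

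**3. Search for the covariate.** The five models together hold age, ethnicity, parity, pregestational BMI, gestational weight gain, history and smoking. The addendum adds no covariate. Stratification uses age, BMI and parity. Entry fasting glucose appears in none of them.

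**4. What adjustment would gain.** The documents do not say how strongly entry fasting glucose predicts GDM, so the odds ratio per SD is an assumption, varied from 1.25 to 3.0. Each setting used 2,000 simulated trials of 315 per arm, with marginal risks of 35% and 24.5%. A treatment-only logistic model was compared with one adding a standardised baseline covariate. The marginal relative risk came from standardising the adjusted model.

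| Assumed OR per SD | Power, crude | Power, adjusted | Variance of marginal log RR, adjusted / crude | SE of log OR, crude → adjusted |
|---|---|---|---|---|
| 1.25 | 81.7% | 82.1% | 0.993 | 0.177 → 0.178 |
| 1.5 | 80.9% | 82.4% | 0.963 | 0.177 → 0.180 |
| 2.0 | 82.0% | 84.5% | 0.922 | 0.177 → 0.186 |
| 2.5 | 82.5% | 88.2% | 0.852 | 0.177 → 0.191 |
| 3.0 | 82.1% | 88.0% | 0.835 | 0.177 → 0.197 |

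Monte Carlo error is about 0.9 points on each power. The gains run from 0.4 to 5.9 points.

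In terms of the standard error: the crude SE of the log relative risk is √[(0.65/0.35 + 0.755/0.245)/315] = 0.125. At the strongest setting it becomes 0.125 × √0.835 = 0.114.

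The last column shows where the gain does not appear. In a logistic model the adjusted log odds ratio has a larger standard error. Its estimate also moves further from 1 (from about 0.60 to 0.59 at OR 1.5 and 0.54 at OR 3.0). The gain is in power and in the marginal relative risk.

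**5. Validity of the crude comparison.** Under no treatment effect, 4,000 trials per setting were simulated with entry values truncated below 92. The assumptions were mean 84, SD 7, correlation between the two tests 0.3 to 0.7, and a case defined as a later value of 92 or more or another route with probability 0.22. Type I error was 4.7% to 5.4% and the mean log relative risk lay between −0.002 and +0.002. The comparison is unbiased.

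**The case against.** **The choice of covariates is the analyst's, and the gain is small.** This largely stands. At odds ratios of 1.25 to 1.5 per SD the gain is at most 1.5 points of power. It is measured against the crude model and would be smaller over Model 5 if BMI, age and history share information with fasting glucose. With 350 per arm the unadjusted power is already about 86%. The point is therefore minor, but the remedy costs almost nothing.

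**A covariate cannot help a test that comes before it.** On its natural reading, the logistic models follow a significant chi-squared result, although the condition could be read as covering secondary outcomes only. A model fitted after that gate cannot raise the power of the test that opens it. This stands and shapes the fix: the adjusted relative risk must be estimated whatever the univariate result.

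**The p < 0.15 screening rule could have admitted it.** That rule is in the protocol's main *Statistical analysis* section. The final analysis section then fixes the models by name, without entry glucose.

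**A stronger reading.** A reader might infer that women enter just under the line that later defines a case, so that test-to-test variation alone produces events and distorts the comparison. The documents do not support this:

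- Women enter anywhere below 92 mg/dl. In the assumed distribution of step 5 only 17% to 19% lay within 4 mg/dl of it.
- The outcome cut-offs are not printed. That one abnormal value suffices is only implied by the remark that "it is important to remember that previous criteria required two abnormal oral glucose tolerance tests".
- Such variation would affect both arms alike, and step 5 shows no bias.
- Adjusting for the entry value would not remove cases caused by error in the later test.

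**Conclusion.** The point holds as a minor missed efficiency and not as a validity flaw. That entry fasting glucose is in none of the listed models, the relative-risk methods or the stratification factors can be read directly from the protocol. So can the fact that eligibility requires it, and that the protocol itself links fasting glucose to the GDM rate.

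The cost of the omission is about 1% to 17% of the variance of the marginal log relative risk, or about 0 to 6 points of power at 315 per arm. This range rests on assumed odds ratios per SD of 1.25 to 3.0 and on the crude analysis as comparator. The simulated relative risk came from a standardised logistic model; robust Poisson regression was not itself simulated.

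**What to change.** In the final *Statistical analysis* section and the April 2017 addendum:

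- Add the 8-12 GW fasting plasma glucose, as a continuous baseline covariate, to the adjusted relative-risk model for the primary outcome. Poisson regression with robust variance, which the addendum already names, would serve.
- State that this model is fitted and reported whether or not the chi-squared test is significant.
- The final analysis section is written in the past tense. If results are already known, label this a supporting analysis and leave the planned comparison as it is.

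A table splitting GDM cases by arm into those met on the fasting value alone and those met on a post-load value is optional.

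The cost is a few words of analysis text and one model run. The covariate is already required for eligibility, so no new test, visit or participant is needed.

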### **Secondary outcome:**

- To define functional genetic risk of developing GDM focusing in obese and non obese pregnant women.
- To investigate the effects of MedDiet and physical exercise/activity scheduled in inflammatory biomarkers in pregnant women.
- To investigate the effects of MedDiet and physical exercise/activity scheduled in the epigenetic mechanisms (DNA methylation and miRNA expression) in pregnant women and offspring; if so, it would represent a novel epigenetic mechanism for regulation of gene expression in the offspring.
- To investigate whether the MedDiet and physical exercise/activity scheduled alters the composition of the gut microbial flora both in women and offspring.
- To evaluate the impact of all these parameters on the long-term health of newborns in the first year of life.
- To estimate changes in HbA1c, insulin, HOMA, lipid profile, body weight, blood pressure, adherence to changes in lifestyle estimated by Med Score and urinary hydroxytyrosol levels and plasma  $\gamma$ -tocopherol levels to confirm compliance in the group receiving MedDiet [extra virgin olive oil (EVOO) and pistachios].
- The parameters to be assessed will be: gestation duration and fetal development; delivery characteristics such as caesarean delivery and instrumental vaginal birth, placental weight; and newborn data such as newborn weight, Apgar test values and cord blood pH.

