### ***Follow-up***

Women will be enrolled at 8-12 GWs (visit 0) and will follow-up at GWs 12-14 (visit 1), 24-28 (visit 2), 34-36 (visit 3) and delivery (visit 4), as well as at 12 weeks (visit 5) and 1 year post delivery (visit 6).

Baseline assessments (Visit 0): Women will be evaluated after the signature of the informed consent form. A complete medical history and physical exam will be performed. Subsequent assessments (Visits 1-6): Women will be followed up by means of clinic visits by the study staff. Six clinic visits will be performed, including: assessment of endpoints/outcome measures, assessments of safety including general (e.g. physical examination), specific safety assessments (e.g. blood chemistries including general biochemistry, hematology and urine analyses) and adverse event collection, assessment of compliance with the study and recording of concomitant medications. Blood and stool samples will be taken at this time. At visit 5 and 6, cord blood and placenta will be taken.

All biological samples will be extracted in one point and will be supervised by a scientist staff that will ensure fit for-purpose operations (high-throughput, high-quality). Design and testing of the sample-handling protocol will consider key factors that could affect the stability of biological samples, including anti-coagulants, stabilizing agents, temperature, and elapsed time from collection to initial processing and endogenous

degrading properties (enzymes). Sample fractions will be stored in two separated ultra-low temperature freezers to ensure long-term stability and integrity.

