# ADENDUM, November 30, 2014

- IG will be provided 10 L of EVOO and 2 kgs of pistachios at 12-14 GWs (Visit 1) for free, to ensure compliance to the intervention of at least 12 weeks before attending GDM screening.
- Pistachios are chosen as nuts for IG, because their consumption can decrease appetite and involve glucose- and insulin-lowering effects. Consequently, serum  $\gamma$ -tocopherol, a biomarker of pistachio intake, will be assessed.
- Adherence biomarkers will be measured at baseline and at 24-28 GW in 10% of participants randomly selected from the IG and CG.
- The 14-point Mediterranean Diet Adherence Screener (MEDAS) will be also used to obtain the MEDAS-derived PREDIMED score (**Figure 3**).
- The study will be single-blinded. The staff involved in the trial (doctors, midwives, evaluator...) might know of the pregnant women's participation in the study, but whether they belong to the CG or IG will remain unknown, excepting to the dieticians. Between 12-14 and 24-28 GWs there will be no visits programmed by the staff of the trial.

Figure 3- MEDAS questionnaire.

| Questions                                                                                                                              | Criteria for 1 point              |
|----------------------------------------------------------------------------------------------------------------------------------------|-----------------------------------|
| 1. Do you use olive oil as main culinary fat?                                                                                          | Sí                                |
| 2. How much olive oil do you consume in a given day (including oil used for frying, salads, out-of-house meals, etc.)?                 | ≥4 tbsp                           |
| 3. How many vegetable servings do you consume per day? (1 serving : 200 g [consider side dishes as half a serving])                    | ≥2 (≥1 portion raw or as a salad) |
| 4. How many fruit units (including natural fruit juices) do you consume per day?                                                       | ≥3                                |
| 5. How many servings of red meat, hamburger, or meat products (ham, sausage, etc.) do you consume per day? (1 serving: 100–150 g)      | <1                                |
| 6. How many servings of butter, margarine, or cream do you consume per day? (1 serving: 12 g)                                          | <1                                |

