**References:**

2. J. Zhang and K. Yu, 1998. What's the Relative Risk, *JAMA*, Vol 280, No 19, pp 1690-1691.
3. Zou G. A Modified Poisson Regression Approach to Prospective Studies with Binary Data. *Am J Epidemiol* 2004; 159(7):702-6. 3

ADENDUM, May 4, 2017

Follow-up.

All participants were followed-up at the obstetrics department throughout the pregnancy. From the 24-28 GW forward, if women from both the CG and IG were diagnosed with GDM, they were followed-up at the Diabetes and Pregnancy Unit. Both groups of women, regardless of belonging to the CG or IG, were given the same lifestyle recommendations to treat the GDM:

Women were advised to avoid or limit the intake of refined carbohydrates, sugary drinks including fruit juices, red meat (particularly processed meat), bakery and pastries. At least 3 servings of skimmed milk dairy products per day, 2 servings of vegetables per day, and 2 servings of fresh fruit instead of juices per day were recommended. Nuts instead of processed meat snack, oily fish, and virgin olive oil daily and whole grain cereals and legumes instead of white cereals and potatoes were also recommended. A leisure-time physically active lifestyle including walking at least 15 minutes, and climbing stairs at least 4 floors, 4 times a day > 5 days per week, were recommended.

On the other hand, both women with and without GDM diagnosis had a regular obstetric care throughout the pregnancy. This was independent to which group they were randomized to.

Therefore, follow-up by the dietician was done with independence to medical care. It did not overlap with scheduled medical visits. However it did coincide with the scheduled appointments in clinical analysis.

- **Control group (CG).** Women were assigned to a standard treatment based on recommendations provided in clinical practice. The main recommendation was to reduce all types of fat from both animal and vegetable sources including nuts and EVOO, and a training program is also provided. This prudent diet recommendation represents a contribution of total fat less than 30% of total energy intake (<40 mL EVOO and not nuts consumption), and carbohydrate intake more than 50%. These

recommendations provided are based on national clinical guidelines, and were provided at Visits 1, 2 and 3 by the midwives.

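### Models 2, 4 and 5 adjust the intervention effect for gestational weight gain, which arises mostly after randomisation, so they do not estimate the intention-to-treat effect and can be biased either way if the diet changes gain

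*Protocol*

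**What the plan says.** In the Protocol, Final statistical analysis, Statistical analysis, the purpose of the models is stated directly: "Logistic regression analyses were used to assess the effect of the intervention". The covariate sets are:

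- Model 1: age, ethnicity, parity.
- Model 2: "model 2 adjusted for pregestational BMI and gestational weight gain (continuous").
- Model 3: gestational, personal and family history, and smoking.
- "Model 4 adjusted for the variables in Models 1 and 2; and Model 5, adjusted for the variables in Models 1-3".

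The same paragraph adds "These models 4 and 5 were only fitted for the primary outcome". The same section says that primary analyses are by intention to treat and that outcomes are compared by chi-squared test. The addendum of April 1, 2017 adds a crude relative risk for each outcome.

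The timing comes from elsewhere in the Protocol. Follow-up: "Women will be enrolled at 8-12 GWs (visit 0"). Addendum of November 30, 2014: "IG will be provided 10 L of EVOO and 2 kgs of pistachios at 12-14 GWs (Visit 1"). GDM is assessed at 24-28 weeks. Secondary outcome lists "To estimate changes in HbA1c, insulin, HOMA, lipid profile, body weight, blood pressure". From 24-28 weeks onward, according to the addendum of May 4, 2017, "if women from both the CG and IG were diagnosed with GDM, they were followed-up at the Diabetes and Pregnancy Unit" and given diet and activity advice. The window over which weight gain is measured is not stated.

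**The concern.** Pregestational BMI is fixed before randomisation. Gestational weight gain is not: most of it comes after enrolment and after the diet has started. The protocol leaves room for the diet to act on it. Body weight is a listed outcome, the appetite effect of pistachios is a reason for choosing them, and the arms differ in planned fat intake (35-40% against less than 30% of energy) and in free food.

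Conditioning on a consequence of treatment does two things. It removes whatever part of the effect runs through weight, and it opens a path through any shared cause of weight gain and GDM, so the compared groups are no longer balanced by randomisation. If gain is counted past the GDM test, there is a third problem: women diagnosed with GDM are then treated with diet and activity, so the covariate is partly a result of the outcome.

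At stake are the adjusted effects, in particular both of the fullest models for the primary outcome. Randomisation was stratified by age, BMI and parity. Model 1 lacks BMI, Model 3 has none of the three, and Models 2, 4 and 5 contain weight gain. So no adjusted model covers the stratification factors without it.

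**Working it through.** **1. The plan's own figure.** Inputs from Sample size: 35% in controls, a 30% relative reduction, 80% power, two-sided 5%. Then p1 = 0.35, p2 = 0.70 × 0.35 = 0.245, and the mean is 0.2975.

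n = [1.96 √(2 × 0.2975 × 0.7025) + 0.8416 √(0.35 × 0.65 + 0.245 × 0.755)]² / 0.105² = (1.267 + 0.541)² / 0.011025 = 296.4, so 297 per group.

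With continuity correction: (296.4 / 4) × [1 + √(1 + 4 / (296.4 × 0.105))]² = 315.2, which agrees with the stated 315. The planning rates can therefore be used as they stand.

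**2. The target effect.** Crude OR = (0.245 / 0.755) / (0.35 / 0.65) = 0.603, with log about -0.51.

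**3. Hand approximation, mediation only.** Let the diet shift gain by d kg and let each kg add b to the log-odds of GDM. Adjusting for gain removes b × d, so the adjusted log OR is about -0.51 - b × d. The documents give neither d nor b. Assume |d| = 1-2 kg and b = 0.05-0.10.

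- Diet lowers gain: -0.51 + 0.05 = -0.46 (OR 0.63) to -0.51 + 0.20 = -0.31 (OR 0.73).
- Diet raises gain: -0.51 - 0.05 = -0.56 (OR 0.57) to -0.51 - 0.20 = -0.71 (OR 0.49).

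**4. Simulation.** Logistic model, 300,000 women per scenario, with intercept and treatment coefficient solved so that the marginal risks are 35% and 24.5%. GDM is then regressed on arm alone and on arm plus gain. The standard deviation (SD) of gain is assumed to be 4-6 kg (5 kg in the second row), with b as above.

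| Assumed situation | Adjusted OR (crude 0.60) |
|---|---|
| Diet lowers gain by 1-2 kg | about 0.62-0.79 |
| Diet raises gain by 1-2 kg | about 0.48-0.57 |
| Diet lowers gain by 1-2 kg and diagnosed women gain 2 kg less afterwards | about 0.52-0.66 |
| Diet does not change gain | about 0.58-0.61 |

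The first row reaches 0.79 only with an unmeasured shared cause of gain and GDM (for example, correlation 0.5 with gain and log-odds 0.5 per SD). Without one it stops at about 0.72, in line with step 3. The second row has no shared cause; one would lower it further. The third row crosses 0.60 because two biases oppose each other, and the balance depends on the SD of gain and the strength of the shared cause.

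**5. On the log scale.** ln 0.60 = -0.511.

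- First row: ln 0.62 = -0.478 and ln 0.79 = -0.236, so 6% to 54% of the log effect is lost.
- Second row: ln 0.57 = -0.562 and ln 0.48 = -0.734, so the log effect is overstated by 10% to 44%.

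**6. Shared cause alone.** In a separate run of 400,000 women, gain had no effect on GDM, but a shared cause did (correlation 0.5 with gain during the diet period, log-odds 0.8 per SD). With the diet lowering gain by 0.3 SD, the OR moved from 0.606 to 0.655. With the diet raising it by 0.3 SD, the OR moved from 0.603 to 0.546. Gain need not be a cause of GDM for the adjustment to distort the comparison.

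**The case against.** The strongest reply is that the primary comparison does not depend on these models. The chi-squared test, the crude OR and the crude relative risk are all free of weight gain, as are Models 1 and 3, and nothing in the protocol names Model 2, 4 or 5 as the confirmatory estimate. That stands. A reader might infer that the trial's intention-to-treat result is compromised; the documents do not support this.

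Second, a reader might infer that the adjusted effects are certainly biased. This is not established either. The secondary-outcome list gives body weight no expected direction, and the appetite remark gives no size. If the diet leaves gain unchanged, the OR hardly moves (0.58-0.61), and the small movement is what adjusting an OR for any prognostic covariate produces.

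Third, reverse causation through GDM treatment needs gain to be counted beyond the 24-28 week test. The protocol states no window, so this is conditional. It would also be wrong to say that such treatment makes the adjusted models exaggerate the benefit: the range of 0.52-0.66 lies on both sides of 0.60.

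What the reply does not remove is that the protocol itself fixes this covariate list, says the models assess the intervention effect, and does not label them as mediation or sensitivity analyses. Nor does having a clean crude result supply a clean model adjusted for the stratification factors.

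**Conclusion.** The point holds for the adjusted estimates. Models 2, 4 and 5 condition on a variable that arises mostly after randomisation and that the diet may change, so they do not estimate the intention-to-treat effect. If the diet changes gain, the distortion can go either way. Under the assumptions shown, an OR of 0.60 could appear as anything from about 0.48 to 0.79; with no diet effect on gain it stays near 0.60. The actual size cannot be known from the protocol, because the effect of the diet on gain, the relation of gain to GDM, the SD of gain and the measurement window are all absent.

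This should be fixed, but it does not invalidate the trial: the crude analyses are sound, and the sample size of 315 per group is unaffected.

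**What to change.** Delete gestational weight gain from Model 2, and so from Models 4 and 5. Keep pregestational BMI and the other covariates fixed before randomisation. Model 4 then contains age, parity, BMI and ethnicity, which covers all three stratification factors, and Model 5 adds history and smoking. If the adjusted relative risks in the April 2017 addendum use the same covariate sets, make the same change there.

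Report weight gain by arm as a secondary outcome. If a model with weight gain is still wanted, label it an exploratory mediation analysis, define the measurement window, and use gain up to the GDM test only.

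Cost: one sentence in the analysis section and a re-run of three models. No new data and no change to the sample size.
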